## Abstract

**Background/Objectives:** This study aims to evaluate the effectiveness of binaural beats (BB) on the autonomic nervous system (ANS), kinesiophobia of reinjury and fitness biomarkers in professional athletes with chronic musculoskeletal injuries. **Methods**: A total of 54 athletes aged 18–25 years, engaged in open-skill sports and experiencing chronic lower-limb injuries for over three months, will be recruited. They will be randomly assigned to one of three groups: an intervention group, a placebo group, and a control group. All athletes will undergo a 15 min auditory intervention five times per week for four weeks. The intervention group will listen to BB embedded in music at high beta and gamma frequencies (30–100 Hz) with guided instructions. The placebo group will receive placebo BB within the same music framework, while the control group will listen only to the music background. Assessments will be conducted at baseline, immediately post-intervention, and at a 4-week follow-up. The primary outcomes will be kinesiophobia of reinjury, ANS function, and heart rate variability (HRV), assessed using the Tampa Scale of Kinesiophobia (TSK-17), Sympathetic Skin Response (SSR), and HRV analysis, respectively. Secondary outcomes will include sport-related anxiety and pain beliefs, assessed using the Sport Competition Anxiety Test (SCAT-15) and the Pain Beliefs and Perceptions Inventory (PBPI-16), respectively; handgrip strength, assessed using the Hand Grip Test; and fitness-related biomarkers, including maximal oxygen uptake (VO_2_max) and blood lactate concentration. **Conclusions**: These findings may provide evidence supporting BB as a complementary, non-invasive intervention to enhance psychological and physiological rehabilitation in injured athletes. Ethics and Dissemination: The study has received ethical approval and is registered on ClinicalTrials.gov. Findings will be disseminated through peer-reviewed publications, conferences, and academic presentations.

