Athletes who participate in open-skill sports were selected because these sports involve unpredictable movement environments, which may increase the risk of lower-limb injury. Therefore, interventions that improve autonomic regulation, such as binaural beats, may help reduce fear of reinjury.

Therefore, based on this theoretical and clinical reasoning, the present study aims to investigate the effects of binaural beat stimulation on kinesiophobia of reinjury, on ANS function through the Sympathetic Skin Response (SSR) and the Isometric Hand Grip test (IHG) and the fitness biomarkers such as VO_2_max, blood lactate concentration, and HRV in professional athletes with chronic lower-limb musculoskeletal injuries (MSK-I). A secondary objective is to examine the maintenance of these effects four weeks after the intervention. It is hypothesized that binaural beats favorably modulate ANS activity, reduce kinesiophobia, reinjury anxiety, and pain beliefs, and enhance aerobic capacity, with sustained effects at follow-up. Conversely, the null hypothesis posits that binaural beat stimulation will not significantly affect ANS function, psychological outcomes, or fitness biomarkers, nor will any effects be maintained after four weeks.

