### 2.2. Procedures

This double-blind randomized controlled trial will investigate the effects of binaural beats on biopsychological outcomes in professional athletes with a history of chronic lower-limb musculoskeletal injuries. The study will be conducted in three phases: baseline (pre-intervention), immediately after the four-week intervention, and four weeks after completion of the intervention. Outcome measures will include self-report questionnaires assessing kinesiophobia, sport-related anxiety, and pain beliefs; physiological assessments of autonomic nervous system (ANS) function; handgrip strength; and fitness-related biomarkers, including maximal oxygen uptake (VO_2_max), blood lactate concentration, and heart rate variability (HRV). All athletes will complete a four-week standardized binaural beats music-based intervention incorporated into the warm-up phase prior to each training session and official game. The BB intervention will be administered 5 times per week (pre-training and pre-game), resulting in a total of 20 sessions. Each session will consist of 15 min of music listening (Figure 1).

Prior to initiating the intervention, athletes will receive detailed oral and written information regarding the study aims and assessment procedures from licensed physiotherapists with five years of clinical research experience. Data collection will include both subjective and objective measures and will be conducted at three time points: baseline (pre-intervention), immediately post-intervention, and four weeks after the completion of the intervention. Written informed consent will be obtained from all participants before enrollment.

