### 2.3. Main Outcome Measures

All questionnaires will be administered in three phases: baseline (pre-intervention), immediately after the four-week intervention, and four weeks after completion of the intervention for all three groups. The questionnaires will assess kinesiophobia, sport-related anxiety, and pain-related beliefs. Final questionnaire scores will be used for statistical analysis, and predefined scoring criteria will be applied where relevant to characterize participants’ baseline psychological status.

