#### 2.3.4. Sympathetic Skin Response: Autonomic Nervous System Function

Autonomic nervous system function will be evaluated through Sympathetic Skin Response (SSR) and through grip strength in two phases: pre-intervention and 4 weeks post–BB intervention for all three groups. Additionally, these procedures will be repeated during the follow-up period.

SSR is a neurophysiological tool designed to assess the functional integrity of the sympathetic cholinergic sudomotor pathways. It is a non-invasive, routine test used to assess autonomic dysfunction, specifically measuring how sweat glands (sudomotor activity) respond to various stimulus, such as electrical or auditory stimulation. SSR testing will be conducted using the Dantec Keypoint system (version 5.13; Alpine Biomed ApS, Skovlunde, Denmark), following the standard protocol [61]. All athletes will be instructed to refrain from smoking and to consume only a light breakfast, excluding alcohol and caffeine. The examination room temperature will be maintained at 23–26 °C, and limb temperature at 32–33 °C. Recordings will be obtained using surface, circular electrodes. The active electrodes will be positioned on the left palm and right sole, while the reference electrodes will be placed on the dorsum of the corresponding hand and foot. Electrical stimuli will be delivered to the right wrist at an intensity of 75 mA and a duration of 0.1 ms. The band-pass filter will be set between 0.5 and 2000 Hz. Five stimuli will be administered unpredictably at random intervals of at least 30 s. Latency will be measured from the onset of the stimulus artifact to the first deflection from baseline (in seconds), and amplitude will be measured peak-to-peak (from negative to positive peak, in millivolts). The shortest latency and the highest amplitude among the five responses will be used for statistical analysis. Parameters included in the analysis will be: SSR upper-limb latency, SSR upper-limb amplitude, SSR lower-limb latency, and SSR lower-limb amplitude (Figure 2, Figure 3 and Figure 4).

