For the assessment of HRV, time-domain indices will be used, including the interval between two successive heartbeats (RR interval), the number of heartbeats per unit of time (HR), the standard deviation of normal-to-normal intervals (SDNN), and the root mean square of successive differences between adjacent intervals (RMSSD). In addition, frequency-domain measures will be analyzed, including the absolute power of heart rate variability in the low-frequency band (LF: 0.04–0.15 Hz) and the high-frequency band (HF: 0.15–0.40 Hz), the ratio of low- to high-frequency power (LF/HF), and total power (TP) [71,72]. For the statistical analysis, mean values of RR intervals (s), mean heart rate (HR; bpm), SDNN (ms), RMSSD (ms), LF (ms^2^), HF (ms^2^), LF/HF ratio (%), and total power (TP; ms^2^) will be used, as recorded during the resting phase and across the three phases of the recovery phase.

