The clinical relevance of the findings was determined using partial eta squared (η^2^) as an index of effect size. Effect sizes were interpreted as small (η^2^ ≥ 0.01), moderate (η^2^ ≥ 0.06), or large (η^2^ ≥ 0.14) [67]. For continuous outcomes, estimated mean differences, standardized effect sizes, exact *p*-values, and corresponding 95% confidence intervals (95% CI) will be reported as appropriate. For categorical outcomes, odds ratios with 95% CI will be reported where applicable. All statistical analyses will be performed using SPSS version 29.0, with statistical significance set at *p* < 0.05.

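### Three unranked primary outcomes, spread over many analysed variables and all tested at 0.05, leave the error rate across the primary set uncontrolled, and sections disagree on where handgrip and HRV belong

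*Protocol article*

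**What the plan says.** **Primary set.** The Abstract says: "The primary outcomes will be kinesiophobia of reinjury, ANS function, and heart rate variability (HRV"), measured by TSK-17, SSR and HRV analysis. It gives no order among the three. It makes handgrip strength and the fitness biomarkers (VO2max, lactate) secondary.

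**Variables analysed.**
- Questionnaires (section 2.3): "Final questionnaire scores will be used for statistical analysis".
- SSR (section 2.3.4): "SSR upper-limb latency, SSR upper-limb amplitude, SSR lower-limb latency, and SSR lower-limb amplitude".
- HRV (Kubios subsection of 2.3.6): mean RR, mean HR, SDNN, RMSSD, LF, HF, LF/HF and total power, "as recorded during the resting phase and across the three phases of the recovery phase".

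**Testing.** Section 2.5 plans a mixed-design ANOVA with Time, Group and their interaction. After a significant effect, pairwise comparisons are adjusted for multiplicity. It closes: "All statistical analyses will be performed using SPSS version 29.0, with statistical significance set at" p < 0.05.

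**Other descriptions of the same measures.** The aims in the Introduction place the effect "on ANS function through the Sympathetic Skin Response (SSR) and the Isometric Hand Grip test (IHG") and list HRV among the fitness biomarkers. Section 2.2 likewise ends its list of fitness measures with "blood lactate concentration, and heart rate variability (HRV"). Section 2.3.4 evaluates ANS function by SSR and grip strength, "in two phases: pre-intervention and 4 weeks post–BB intervention for all three groups", with a further repeat at follow-up.

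**The concern.** With several primary outcomes, no hierarchy and a flat 0.05, the stated significance level describes each test but not the set of primary conclusions. The post hoc adjustment does not help: it starts only after one variable's omnibus test has passed and never looks across variables. The null hypothesis in the Introduction is global, covering ANS function, psychological outcomes and fitness biomarkers together, so an isolated significant result could be read as evidence against it.

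The shifting place of handgrip, and less sharply of HRV, adds to this. A reader cannot tell from the article alone exactly which measures make up the primary set.

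**Working it through.** **1. The plan's own figure.** Section 2.1 gives a minimum of 48 for a 3 × 3 mixed ANOVA with f = 0.25, alpha 0.05 and power 0.95. For the group-by-time interaction, λ = f²·N·m/(1 − ρ), with df1 = (k − 1)(m − 1) = 4 and df2 = (N − k)(m − 1) = 90 at N = 48.
- ρ = 0.5: λ = 0.0625 × 48 × 3 / 0.5 = 18, power 0.930; 54 would be needed with equal groups.
- ρ = 0.55: λ = 9 / 0.45 = 20, power 0.954, and 48 suffices.

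The article does not state ρ, so 48 is reachable and is not shown to be wrong. Dropout: 48 / 0.9 = 53.3; rounded up to equal groups this is 54, as stated. What matters here is that the calculation covers one test at 0.05 and names no outcome.

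**2. Count of primary variables.**
- One variable per domain: 3.
- HRV phase treated as a within-subject factor: 1 + 4 + 8 = 13.
- HRV phases analysed separately: 1 + 4 + 8 × 4 = 37.

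The article does not say which HRV treatment applies.

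**3. Chance of at least one false-positive interaction if the tests are independent,** 1 − 0.95ⁿ:
- n = 3: 1 − 0.95³ = 14.3%
- n = 13: 1 − 0.95¹³ = 48.7%
- n = 37: 1 − 0.95³⁷ = 85.0%

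The expected number of false positives is 0.05n whatever the correlation: 0.15, 0.65 and 1.85.

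**4. Allowing for correlation.** The article gives no correlations, so all of these are assumptions. The figures are simulated under no effect. *Common* means one correlation among all variables. *Block* means correlation only within the SSR set and within the HRV set. *Index × phase* gives HRV one correlation between indices and one between phases, both set to the value shown, and gives SSR the same value.

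| Correlation | 3 variables, common | 37, common | 37, block | 37, index × phase |
|---|---|---|---|---|
| 0.3 | 13.6% | 72% | 75% | – |
| 0.5 | 12.6% | 55% | 64% | 71% |
| 0.7 | 10.9% | 37% | 50% | 57% |
| 0.8 | – | – | 40% | 45% |
| 0.9 | – | – | 30% | 34% |

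Only the interaction is counted. Section 2.5 also tests Group and Time main effects for every variable, and these are left out.

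**5. Classification side by side.**

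| Measure | Abstract | Elsewhere |
|---|---|---|
| Handgrip | Secondary | Part of ANS function (Introduction aims; 2.3.4), which the Abstract makes primary |
| HRV | Primary | Grouped with fitness biomarkers (Introduction aims; 2.2), which the Abstract makes secondary |

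**The case against.** The best case on the other side has five parts.

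- **No text labels 37 variables as primary.** Correct. The count assumes that the HRV phases are separate outcomes; if phase is a factor it is 13. The finding does not depend on 37, because three variables already exceed 5%.
- **Independence is unrealistic.** Also correct. Mean RR and mean HR are near-reciprocals, LF/HF is built from LF and HF, and total power contains both. A reader might infer from 85% that a false-positive primary result is likely. That needs low to moderate correlation; at 0.7 the figure is 37–57% depending on structure, and at 0.9 about 30–34%.
- **No rule says that any one result, at any visit, makes the trial positive.** True. The Discussion's hypothesis expects psychological and autonomic changes together. The interaction is one omnibus test over all visits, so visits add no tests to the count. A reader might also infer that the primary could be picked after the results are seen; the article leaves the choice open but shows no such intent.
- **Only the Abstract ranks outcomes.** The Introduction and section 2.2 group HRV by topic, and the Kubios subsection calls it an indicator of ANS activity. For HRV this is a wording mismatch. For grip it is a real inconsistency, because 2.3.4 names grip as a means of evaluating a primary domain. The visit wording in 2.3.4 and 2.3.6 is most naturally loose phrasing for the end of the four-week course and does not show a different schedule.
- **An analysis plan may set a hierarchy.** It may. The point rests on what the article fixes, namely several primaries and a flat 0.05. An unseen plan cannot make the article's sections agree.

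**Conclusion.** The concern holds in this form: the article names three unranked primary outcomes, gives two of them several analysed variables, tests all at 0.05, and adjusts only within each ANOVA. Following it as written puts the false-positive risk across the primary set at about 11–14% at the least (one variable per domain, correlations 0 to 0.7). It rises to at most about 49% for 13 variables, that being the independence figure. For 37 variables it is 85% under independence and roughly 30–50% at correlations of 0.7–0.9, with one assumed structure reaching 57% at 0.7. Where in this range the trial sits depends on correlations and on an HRV treatment that the article does not give. Well above 5% is supported; a specific high figure is not. The grip classification contradicts the Abstract, while the HRV grouping and the visit wording need only be aligned.

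**What to change.** **Preferred.** Name one primary variable. The TSK-17 total is the natural candidate because it is named first. Test it by the planned group-by-time interaction at 0.05, which keeps the basis of the sample size in section 2.1 and returns the primary error rate to 5%. Follow it with the multiplicity-adjusted experimental-versus-placebo contrast, since a three-group interaction does not by itself isolate the beats. Name one SSR and one HRV variable as key secondaries, in fixed order or by Holm, and label the remaining variables exploratory.

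The interaction should not be replaced as primary test by a two-arm, single-visit comparison without repricing. With 48 / 3 = 16 per arm, power would be about 28% at d = 0.5 and 59% at d = 0.8 (assumed effects).

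**Alternative.** Keep three primaries, one variable each, with Holm or Bonferroni, and restate power. At the Bonferroni level 0.05 / 3 = 0.0167, with f = 0.25 and assumed ρ = 0.5, power is about 85% at N = 48 and 90% at N = 54; 95% would need 66 analysed. Spreading Bonferroni over all 37 variables is not practical: power per variable falls to about 57% at N = 48.

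**In either case,** state whether HRV phases are separate outcomes or a factor. Align the place of grip and HRV across the Abstract, Introduction, 2.2 and 2.3.4, and align the visit wording in 2.3.4 and 2.3.6 with the three visits in 2.2.

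**Cost.** The preferred route changes wording only and needs no extra participants, but fewer variables can carry a confirmatory claim. The alternative keeps three such claims at lower stated power.

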## 1. Introduction

Musculoskeletal injuries (MSK-I) represent the most prevalent type of injury among athletes and are associated with substantial physical, psychological, and social consequences that can delay or compromise return to sport (RTS) [1]. The etiology of MSK-I is multifactorial, involving a complex interaction between intrinsic factors—such as sex, age, previous injury history, neuromuscular imbalances, and psychological traits—and extrinsic factors, including training load, technical execution, playing surface, equipment, and environmental conditions [2,3,4]. Epidemiological studies consistently demonstrate that professional athletes sustain injuries more frequently than amateur athletes, largely due to higher training volumes, increased physical and energetic demands, and intensified competitive schedules [5,6].

Injury mechanisms vary according to sport-specific demands, with contact actions (e.g., tackling) and complex, high-speed, multi-joint movement patterns (e.g., throwing while jumping or cutting maneuvers) being among the most common contributors [7,8]. Consequently, both injury incidence and anatomical distribution differ considerably across sports disciplines. Athletes participating in open-skill sports such as football, volleyball, basketball, etc., characterized by unpredictable and externally driven environments, exhibit higher injury rates compared with those engaged in closed-skill sports such as swimming, tennis, martial arts, etc., which involve more stable and predictable movement contexts [9]. For example, professional football reports approximately 8.1 musculoskeletal injuries focused on lower limbs per 1000 exposure hours, whereas swimming reports around 1.54 injuries per 1000 h [10,11]. A recent systematic review indicated that athletes participating in open-skill sports (e.g., basketball, handball, and volleyball) exhibit a higher incidence of lower-limb injuries compared to injuries in other body regions. The most frequently reported injuries in these athletes involve the knee and ankle [12].

Considering the distinct characteristics and demands of open-skill versus closed-skill sports, the present study focused on open-skill athletes because these sports, such as football, basketball, handball, and volleyball, are characterized by unpredictable movement environments, rapid decision-making, opponent interaction, and frequent cutting, jumping, and landing actions. All these sports are associated with an increased risk of lower-limb injury [9]. The heightened cognitive demands inherent to open-skill sports may further elevate injury risk, as athletes are required to continuously engage attentional control, decision-making, and cognitive flexibility, particularly under conditions of fatigue or competitive pressure [13]. These factors may compromise optimal motor execution and neuromuscular control during sport-specific tasks. Accordingly, fear of reinjury is particularly relevant in open-skill athletes during the return-to-sport process, as psychological readiness may directly influence movement confidence, functional performance, and safe reintegration into competitive activity.

Recent consensus-based recommendations in sports injury rehabilitation emphasize that return-to-sport decision-making should be considered a multidimensional and biopsychosocial process, integrating physical recovery, psychological readiness, contextual factors, and risk-management considerations [13,14]. Within this framework, interventions targeting fear of reinjury, autonomic regulation, and psychophysiological readiness may be clinically relevant adjuncts to conventional rehabilitation approaches.

Return to Sports (RTS) process is influenced by an intricate interplay of physical recovery, psychological readiness, and social context [15,16]. Notably, a substantial proportion of athletes experience reinjury upon returning to training or competition, highlighting the limitations of approaches that focus exclusively on physical rehabilitation [17]. Among the biopsychosocial factors affecting RTS outcomes, kinesiophobia has emerged as a critical determinant. A recent systematic review identified kinesiophobia as one of the most influential psychological consequences of sports injuries, significantly contributing to reinjury risk and negatively affecting physical performance, emotional state, and self-confidence [18].

Kinesiophobia is defined as an excessive, irrational fear of movement or physical activity stemming from a perceived vulnerability to pain or reinjury [18]. Elevated levels of kinesiophobia have been positively associated with anxiety, depressive symptoms, attentional disturbances, and reduced self-efficacy during RTS [19,20]. In athletes following anterior cruciate ligament (ACL) reconstruction, kinesiophobia—alongside pain, anxiety, depression, and low self-esteem—has been shown to impair RTS and increase reinjury likelihood across multiple sports, including football, basketball, handball, and rugby [17,19]. Similarly, chronic ankle instability has been linked to heightened kinesiophobia and diminished functional capacity in athletic populations [21]. The Tampa Scale of Kinesiophobia (TSK) is widely used to quantify fear of movement in injured athletes and has demonstrated strong psychometric properties across sports and clinical contexts [22].

Beyond psychological factors, MSK-has been shown to influence central and peripheral nervous system functioning, particularly the Autonomic Nervous System (ANS). Emotional and cognitive responses to injury can modulate ANS activity, shifting the balance between sympathetic (“fight-or-flight”) and parasympathetic (“rest-and-digest”) responses [23]. Cardiovascular regulation, vasomotor activity, and electrodermal responses represent key physiological pathways through which emotional stress and pain-related cognitions manifest following injury [24]. Heart rate variability (HRV) and sympathetic skin response are widely recognized as sensitive indicators of ANS function and autonomic balance [24]. Studies demonstrated that the Isometric Hand Grip Test (IHG) can be a supplementary test to assess autonomic nervous system regulation through metrics the changes in heart rate and blood pressure during implementation is isometric contraction at 30% MVC [25,26].

Emerging evidence suggests that pain intensity, pain catastrophizing, and perceived disability following injury and chronic pain are closely associated with alterations in HRV, reflecting dysregulation of autonomic control [27,28]. Conversely, findings in elite football players indicate a transient increase in HRV approximately 72 h post-injury, suggesting enhanced parasympathetic activation during early recovery [29]. Despite these insights, the relationship between ANS function and kinesiophobia in injured athletes remains largely unexplored.

Hand Grip Strength (HGS) performance elicits acute ANS activation leading to increases in heart rate, blood pressure, and respiratory rate [30,31]. Hand grip test performance may be indirectly influenced by fear, anxiety, or pain anticipation, particularly in athletes recovering from injury, potentially confounding performance outcomes [32]. Recent studies have highlighted a potential link between handgrip strength and mental health outcomes, suggesting that HGS may reflect psychological well-being [33,34]. Liyan, [33] assessed that higher handgrip strength appears to be associated with a lower likelihood of developing generalized anxiety and depressive disorders. Priyadharsan et al, [34] assessed the effect of examination stress on skeletal muscle function among first-year medical students using the HGS test and demonstrated that Maximum Voluntary Contraction (MVC) and endurance time were significantly reduced during the stress state compared to the relaxation state. Despite these insights, the relationship between stress on skeletal muscle function and kinesiophobia in professional athletes with previous lower-limb injuries remains largely unexplored.

Contemporary rehabilitation approaches increasingly emphasize the integration of physical and psychological interventions to address the multidimensional consequences of sports injuries. Programs combining therapeutic exercise, cognitive–behavioral strategies, and pain neuroscience education have demonstrated efficacy in reducing kinesiophobia and improving functional outcomes [35]. Mind–body interventions have been shown to enhance mindfulness, pain resilience, and emotional regulation, thereby supporting RTS [35]. Additionally, psychosomatic interventions such as music or acoustic signal interventions have been proposed as promising strategies to alleviate kinesiophobia and enhance athletic performance [18].

Acoustic signals or music-based interventions delivered through auditory stimuli, stimulating the auditory nerve and activating the brain’s cortex, can be applied during training or prior to competition. They have been shown to positively influence psychophysiological states by modulating emotional, cognitive, behavioral, and physiological responses [36,37]. In athletes, music-based interventions have been associated with improvements in aerobic and anaerobic capacity, as well as enhanced cardiovascular and hormonal regulation, increased motivation, better emotional control, and reduced perceived exertion and fatigue [38,39,40]. However, the effects of acoustic signals or music-based interventions such as binaural beats on kinesiophobia and reinjury prevention following sports-related MSK-I remain insufficiently investigated.

Binaural beats (BB) are an auditory phenomenon often layered with background music and referred to as binaural music. BB occurs when two tones of slightly different frequencies are presented separately to each ear. The brain then perceives a third tone, known as a binaural beat, which equals the difference between the two frequencies. For instance, if one ear hears a tone at 300 Hz and the other at 306 Hz, the brain detects a binaural beat of 6 Hz [41]. Binaural beats require the use of headphones so that each frequency reaches only one ear. The sound of binaural beats is created by the brain rather than by the physical mixing of sound waves in the air; they are perceived binaurally and are often experienced as stronger, associated with the induction of specific brainwave states [41]. BB have gained attention for their potential psychological and physiological effects, particularly in stress modulation and attentional control by using different frequencies (such as delta, theta, beta, alpha and gamma waves). In athletic contexts, binaural beats have been suggested to reduce pre-competition anxiety and enhance concentration, which may be especially beneficial during rehabilitation and RTS [42,43,44]. Physiologically, binaural beats appear to influence ANS activity by modulating sympathetic–parasympathetic balance. Listening to theta-frequency binaural beats post-exercise has been shown to increase HRV, indicating enhanced parasympathetic activation and relaxation [45]. Similar findings have been reported in stress-recovery contexts among military personnel [46]. Evidence examining the effects of binaural beats on kinesiophobia, ANS activity, reinjury anxiety, pain beliefs, and fitness biomarkers in athletes with chronic musculoskeletal injuries remains limited.

Binaural beats constitute a non-invasive form of auditory stimulation that may modulate athletes’ psychophysiological state by influencing cortical oscillatory activity, arousal regulation, and ANS function [41,44,45]. This mechanism is particularly relevant to kinesiophobia, which extends beyond maladaptive beliefs to encompass anxiety, heightened threat perception, increased physiological arousal, and ANS dysregulation. Consequently, binaural beats may reduce fear-related responses by promoting autonomic balance, enhancing psychological readiness, and supporting confident movement.

Athletes who participate in open-skill sports were selected because these sports involve unpredictable movement environments, which may increase the risk of lower-limb injury. Therefore, interventions that improve autonomic regulation, such as binaural beats, may help reduce fear of reinjury.

Therefore, based on this theoretical and clinical reasoning, the present study aims to investigate the effects of binaural beat stimulation on kinesiophobia of reinjury, on ANS function through the Sympathetic Skin Response (SSR) and the Isometric Hand Grip test (IHG) and the fitness biomarkers such as VO_2_max, blood lactate concentration, and HRV in professional athletes with chronic lower-limb musculoskeletal injuries (MSK-I). A secondary objective is to examine the maintenance of these effects four weeks after the intervention. It is hypothesized that binaural beats favorably modulate ANS activity, reduce kinesiophobia, reinjury anxiety, and pain beliefs, and enhance aerobic capacity, with sustained effects at follow-up. Conversely, the null hypothesis posits that binaural beat stimulation will not significantly affect ANS function, psychological outcomes, or fitness biomarkers, nor will any effects be maintained after four weeks.

